**Primary outcome**						
Mindfulness	FMI				x	
**Secondary outcomes**						
Mindfulness	FMI		x	x		x
Depressive symptoms	PHQ-9		x	x	x	x
Anxiety	GAD-7		x	x	x	x
Stress	PSS-4		x	x	x	x
Well-being	WHO-5		x	x	x	x
Presenteeism	PSS		x		x	x
Interoceptive sensibility	BPQ		x		x	x
Self-efficacy	SES		x	x	x	x
Cognitive fusion	CFQ-D		x	x	x	x
Emotion regulation	ERQ		x	x	x	x
Alexithymia	TAS-20		x	x	x	x
Intervention adherence	Intervention dropout			x	x	x
Intervention satisfaction	CSQ-8				x*	
Side effects of intervention	INEP*				x	x
**Covariates**						
Demographic variables	SRQ		x			
Previous experience with mindfulness, use of additional treatment options	SRQ		x		x	x
Treatment expectation	CEQ		x			

*Note.*
*CEQ* Client Expectancy Questionnaire, *CFQ-D* Cognitive Fusion Questionnaire, *CSQ-8* Client Satisfaction Questionnaire, *German Version* ZUF-8, *ERQ* Emotion Regulation Questionnaire, *FMI* Freiburg Mindfulness Inventory, *GAD-7* Generalized Anxiety Disorder Questionnaire, *INEP* Inventory for the Assessment of Negative Effects of Psychotherapy, *BPQ* Body Perception Questionnaire, Awareness Section, *PHQ-9* Patient Health Questionnaire, *PSS* Presenteeism Scale for Students, *PSS-4* Short Form Perceived Stress Scale, *SES* Self-Efficacy Scale, *SRQ* Self-Report Assessment Questionnaire, *TAS-20* Toronto-Alexithymia Scale, *WHO-5* World Health Organization Well-Being Index

*Intervention groups only (UG, GoD)

#### Primary outcome: mindfulness at post-treatment (t2)

The 14-item short scale of the Freiburg Mindfulness Inventory [56] is used to assess mindfulness. The FMI consists of a 4-point scale ranging from 1 = “rarely” to 4 = “almost always.” The short scale demonstrated sensitivity to change [56] and high internal consistency (*α* = 0.84) [65].

#### Secondary outcomes

##### Mindfulness at intermediate assessment (t1) and follow-up (t3)

Mindfulness is also measured after 4 weeks and 6 months.

##### Depressive symptoms

The depression module of the Patient Health Questionnaire [66] comprises of nine items that are rated on a 4-point scale (0 = “not at all” to 3 = “nearly every day”). The PHQ-9 is a widely used depression screening that has been shown to be a valid instrument [67] with good diagnostic properties and excellent internal consistency (*α* = 0.89). It has also been evaluated as an online version [68].

##### Anxiety

The 7-item Generalized Anxiety Disorder Questionnaire [69] is a screening instrument for generalized anxiety disorder and ranges from “not at all” (= 0) to “nearly every day” (= 3). The GAD-7 has been identified to be a reliable and valid measure of anxiety in the general population with a high internal consistency of Cronbach’s *α* = 0.89 [70].

##### Stress

The Short Form Perceived Stress Scale (PSS-4), derived from the Perceived Stress Scale [71], will be used to measure the participants’ perceived stress as the degree to which situations in one’s life are rated as stressful (scale ranging from 0 = never to 4 = very often). The psychometric properties of the PSS-4 have been found to be acceptable and reliable across cultures, with *α* = 0.77 [72].

##### Well-being

The well-established 5-item World Health Organization Well-Being Index (WHO-5) [73] is used to assess subjective psychological well-being. The scale ranges from “at no time” (= 0) to “all of the time” (= 5). Good psychometric properties of the WHO-5 as a screening tool for depression have been demonstrated among diverse clinical studies. Clinical validity has been identified as very high [74].

##### Presenteeism

As academic outcomes, presenteeism, loss of productivity, and absenteeism are assessed using a modified version [46] of the Presenteeism Scale for Students [75]. Presenteeism is measured by the subscale for work impairment (Work Impairment Scale; 10 items, scale 1–5, range 10–50). Productivity losses will be assessed by an adaption of the Presenteeism Scale for Students’ work output scale, investigating the current percentage to which participants were able to reach their usual academic productivity (visual analogue scale ranging from 0% = completely unproductive to 100% = full productivity). Additionally, hours of absenteeism are inquired. For the Work Impairment Scale, a Cronbach’s *α* of 0.90 as well as sufficient test-retest reliability and criterion-related validity could be demonstrated [75].

##### Interoceptive sensibility

Interoceptive sensibility (IS) is assessed by the awareness section of the Body Perception Questionnaire (BPQ) [76]. The section includes 54 items of subjective identifications of bodily signals on a 5-point scale, ranging from “never” (= 1) to “always” (= 5). High scores reflect poor IS. For the short form of the BPQ, categorical omega coefficients between 0.77 and 0.96 as well as high retest reliability were shown [77].

##### Subjective side effects and adverse events

The Inventory for the Assessment of Negative Effects of Psychotherapy (INEP) [78] assesses any changes experienced during or after the treatment in the social and/or work environment and whether they are attributed to the psychotherapeutic intervention. Four items are rated on a 7-point bipolar scale (− 3 = “worse,” + 3 = “better”); the others are rated on a 4-point scale (0 = “no agreement,” 3 = “full agreement”). In the present trial, an adapted 22-item version covering possible negative effects associated specifically with online-trainings (e.g., concerns about data protection) will be applied. The original scale has demonstrated high internal consistency with a Cronbach’s *α* of 0.86 [78].

##### Intervention satisfaction and adherence

The Client Satisfaction Questionnaire (CSQ-8) [79] is a validated 8-item instrument and is used in a version adapted for the evaluation of IMIs [80]. It comprises of eight items, each with a 4-point scale of specific response alternatives (e.g., 1 = “quite unsatisfied,” 4 = “very satisfied”). Good psychometric properties have been demonstrated including Cronbach’s *α* between .88 and .92 [81]. To operationalize intervention adherence, the number of completed modules is assessed. “Per protocol” adherence is operationalized by the percentage of participants that completed at least 5 of the 7 modules 8 weeks after randomization (t2). Additionally, quantitative and qualitative data are collected on participants’ satisfaction with various aspects of the intervention (e.g., number and length of modules, SMS-Coach, practicability in daily life) using self-constructed items (e.g., “Which elements did you find particularly helpful?”).

##### Use of GoD, subscription to SMS coach, and practice of mindfulness exercises

The number of times participants of the GoD condition contact their e-coach will be documented. We will also track whether participants of both intervention groups subscribe to the SMS-coach. Finally, we will assess the weekly time that participants spent practicing the mindfulness exercises introduced to them in the modules (retrospectively at t2).

#### Potential mediators

##### Self-efficacy

Perceived general self-efficacy is measured by the 10-item Self-Efficacy Scale [82] on a 4-point response scale from “1 = not at all true” to “4 = very true.” It was used in numerous research projects, where it demonstrated internal consistencies of Cronbach’s *α* = 0.75–0.91. It has also been proven reliable and valid in various field studies [83].

##### Cognitive fusion

In ACT, cognitive fusion is defined as the extent to which individuals identify with and are behaviorally regulated by their own thoughts and beliefs. Therefore, it is an important aspect of Psychological Inflexibility, which the intervention aims to reduce. It is assessed with the German version of the Cognitive Fusion Questionnaire [84]. Participants are asked to rate the seven items of the CFQ-D on a 7-point scale ranging from “1 = never true” to “7 = always true.” The CFQ-D has demonstrated good psychometric properties reflected in a Cronbach’s *α* of 0.95 as well as convergent validity with measures of physical and mental health [84].

##### Emotion regulation

The Emotion Regulation Questionnaire (ERQ) [85] is used to assess individual differences in habitual use of two emotion regulation strategies, reappraisal and suppression. Participants are required to indicate whether they agree with each statement on a 7-point scale ranging from 1 (= strongly disagree) to 7 (= strongly agree). The ERQ demonstrates good scale score reliability for the suppression (Cronbach’s *α* = 0.76) as well for the reappraisal factor (Cronbach’s *α* = 0.74) [86].

##### Alexithymia

The Toronto-Alexithymia Scale (TAS-20) [87, 88] is used to measure alexithymia. The questionnaire consists of 20 items rated on a 5-point scale (1 = strongly disagree; 5 = strongly agree) with total scores ranging from 20 to 100, reflecting three factor scales: “difficulties identifying feelings” (DIF), “difficulty describing feelings” (DDF), and “externally oriented thinking” (EOF). Higher scores on the different subscales indicate higher levels of alexithymia. The TAS-20 is a valid instrument with good internal consistency (Cronbach’s *α* = 0.85–0.86) and test-retest reliability [89].

#### Covariates

To investigate potential effect-modifying influences [90], several sociodemographic as well as other variables are assessed: age, gender, nationality, marital status, study course and number of semesters, previous experience with mindfulness, psychotherapy experience, and use of additional treatment options (such as psychological counseling or psychotherapy) as well as baseline symptomatology. To examine the influence of treatment expectations on outcomes, the Client Expectancy Questionnaire (CEQ) is used, which has demonstrated high internal consistency (*α* = 0.84–0.85) [91]. It consists of six items which are measured on a 9-point Likert Scale with higher scores representing positive expectations and credibility.

### Sample size estimation

Sample size calculations refer to detect an expected increased efficacy of StudiCare-M unguided and GoD compared to WL on the primary outcome mindfulness at t2 (post-treatment). In their meta-analysis, Spijkerman et al. (2015) found a small effect for unguided mindfulness IMIs (*g* = 0.22, 95% CI 0.10–0.34) and a significantly larger effect for guided IMIs (*g* = 0.43, 95% CI 0.30–0.56) [25]. The GoD version of our IMI provides the possibility to contact an e-coach at any time. Additionally, both the GoD and unguided versions contain various persuasive e-health technologies and that have been shown to increase efficacy and adherence (e.g., self-monitoring, goal setting, SMS prompts, automatic reminders) [63, 92]. Therefore, we assume an effect size comparable to the effects previously found for guided IMIs of *d* = 0.40. Originally, a power analysis based on a two-tailed t-test (calculated using G*Power [93]) resulted in a sample size of 133 participants per group. This was documented in the first version of the trial registration. However, in the meantime, a more precise power calculation was done by an independent biostatistician (MM). This calculation indicates that 129 participants per group are required to obtain a power of 1-beta = 90% based on *α* = .05 (taking into account clustering of participants by university and assuming an ICC = .02). Trial registration was updated accordingly. As data analysis will be based on intention-to-treat (ITT) principles, increasing sample size in order to compensate for drop-outs is not necessary.

Concerning an exploratory comparison between the UG and GoD version of StudiCare-M, the sample size is sufficient to detect a small effect of *d* = 0.20 as minimal clinically important effect difference with a power of 50% and a significance level of *α* = .05. This also corresponds to the range of effect sizes of *d* = 0.02–0.33 found for different outcome measures in the trials of Berger et al. [35] and Rheker et al. [36].

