### Statistical analyses

All data analyses will be performed after completion of data collection. Interim analysis is not considered necessary as in the context of IMIs, there are no known dangers or harms that could make a trial stop necessary. Analyses will be performed on an intention-to-treat basis. Procedures of imputation will be chosen based on patterns and mechanisms of missingness (e.g., by using multiple imputation). Additionally, per protocol analyses (based on the data of participants that completed at least 5 of the 7 core modules) will be performed to examine the impact of drop-outs on study results. Significance level for all analyses will be defined as alpha = .05. A blinded analysis of primary and secondary outcomes will be conducted by an independent researcher not otherwise involved in the execution of the study (MM).

The primary outcome FMI at t2 will be analyzed by means of linear regression models. Baseline and group will be defined as predictors. Secondary outcomes will be analyzed accordingly. Standardized mean differences with 95% confidence intervals will be calculated post-treatment and follow-up to analyze between-group effect sizes. To obtain the number of participants achieving reliable improvement in mindfulness (FMI), participants will be coded as responders and nonresponders according to the Reliable Change Index (RCI) for t2 and t3 [94]. Additionally, we will investigate potential negative effects on individual level by calculating the number of participants that display a reliable deterioration from t0 to t2 and t3 also using the RCI [95, 96]. For an exploratory examination of associations between adherence, subscription to SMS-coach, actual use of GoD, time spent practicing mindfulness exercises, and the primary outcome FMI at t2 regression analyses will be conducted.

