## Discussion

Psychological problems in college students are widespread and associated with poorer academic performance. Internet-based interventions (IMIs) for enhancing mindfulness are a promising way to increase student mental health but typically suffer from low adherence, compromising the effectiveness of such interventions. This trial will be the first to examine the effectiveness of a mindfulness IMI without and with guidance-on-demand, comparing both versions to a waitlist control group as well as to each other. Additionally, we will investigate potential moderators and mediators, an area that is still understudied [25, 99].

Despite best efforts, any trial comes with certain limitations that are described in the following.

A common problem with internet-based interventions is high dropout-rates concerning both intervention and assessments. For unguided mindfulness IMIs, intervention dropout rates of 40–60% have been reported suggesting that only about half of the participants complete such interventions [29, 31]. In order to overcome this problem, we will implement the following measures: an optional SMS-Coach prompting participants every other day; the possibility to contact an e-coach any time in the “GoD” condition; and short automated feedback messages after each completed module in the “unguided” condition. Additionally, in order to receive an estimate of the true treatment effect unbiased by assessment dropout, data will be analyzed on ITT basis [100].

Within the framework of our intervention, we will not be able to track the actual amount and frequency of mindfulness practice participants will engage in. Studies have shown that the time spent practicing mindfulness in daily life is an important moderator of intervention efficacy [18]. We will however ask for the average time participants spent practicing at post-assessment and conduct a moderator analysis based on that information. Still, this retrospective assessment might be biased and a future version of StudiCare-M should include immediate tracking of mindfulness practice, e.g., in an accompanying app.

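### ITT is given as the reason for no drop-out allowance and for an estimate free of assessment-dropout bias; it supports neither, and 90% power on the stated basis presumes complete t2 FMI

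*Protocol article*

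**What the plan says.** The Sample size estimation section powers each intervention arm against the waitlist on FMI at t2, and for the effect states "we assume an effect size comparable to the effects previously found for guided IMIs of *d* = 0.40". It reports two calculations. The first, "a power analysis based on a two-tailed t-test", "resulted in a sample size of 133 participants per group". The second, which allows for clustering by university with an ICC of .02, found that "129 participants per group are required to obtain a power of 1-beta = 90% based on *α* = .05". The abstract's total of 387 is 3 × 129, so nothing has been added for missing data. The reason given is that under ITT "increasing sample size in order to compensate for drop-outs is not necessary".

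The Discussion names high dropout, from assessments as well as from the intervention, as a common problem in this field. It then says: "in order to receive an estimate of the true treatment effect unbiased by assessment dropout, data will be analyzed on ITT basis".

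The Statistical analyses section does provide for missing values: "Procedures of imputation will be chosen based on patterns and mechanisms of missingness", with multiple imputation as an example. The primary model is a linear regression of t2 FMI on baseline and group.

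**The concern.** Both statements credit ITT with something it does not do. Keeping every randomised participant in the assigned arm protects the comparison that randomisation set up. It says nothing about the value of a questionnaire that was never returned. Valid multiple imputation carries the missing information into the standard error, so power still depends on how many t2 scores are observed and how well other data predict the rest. Whether the estimate is unbiased depends on why scores are missing and on the imputation model, for example missing at random given the variables in that model. The observed data cannot confirm such an assumption.

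A reader could therefore take both the 90% power and the absence of dropout bias at face value, for the primary endpoint of an open-label trial with self-reported outcomes.

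**Working it through.** **Inputs.** From Sample size estimation: d = 0.40, α = .05, power 90%, ICC = .02, 129 per group. Two-sided testing is stated there for the earlier calculation and carried over here. From Statistical analyses: adjustment for baseline. Not in the document, so assumed: the fraction m of t2 FMI missing (10 to 40%, equal in both arms) and the baseline–t2 correlation r (0.4 or 0.5).

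**Step 1: reproduce the plan's figures.** On the standardised scale (SD = 1),

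n = 2 × ((1.960 + 1.282) / 0.40)² = 131.3 per group (normal approximation).

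The exact two-sided t-test needs 132.3, hence 133, which is the earlier figure. With individual randomisation inside universities, the between-university share of variance drops out of the comparison, so the variance is multiplied by 1 − 0.02:

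131.3 × 0.98 = 128.7, hence 129, which is the current figure.

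Power at 129 is then 90.1% by the normal approximation, or 89.8% using the t distribution. Neither a one-sided test (108) nor a cluster design-effect inflation with about 15 universities (about 174 to 196) gives 129. Both stated figures need an observed t2 FMI from every randomised participant.

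**Step 2: power with missing t2 FMI.** Observed n per arm is 129 × (1 − m), rounded. The noncentrality is 0.40 / (σ√(2/n)), with σ² = 0.98 unadjusted and σ² = 0.98 × (1 − r²) with baseline adjustment. Power is from the noncentral t, two-sided .05.

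| Missing (assumed) | Observed n per arm | Unadjusted | Adjusted, r = 0.4 | Adjusted, r = 0.5 |
|---|---|---|---|---|
| 10% | 116 | 87% | 92% | 94% |
| 20% | 103 | 82% | 88% | 92% |
| 30% | 90 | 77% | 84% | 88% |
| 40% | 77 | 70% | 78% | 82% |

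The normal approximation gives values within about one point of these.

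**Step 3: where 90% is lost under baseline adjustment.** The n needed for 90% is 128.7 × (1 − r²).
- r = 0.4: 128.7 × 0.84 = 108.1, so up to 1 − 108.1/129 = 16% may be missing.
- r = 0.5: 128.7 × 0.75 = 96.5, so up to 1 − 96.5/129 = 25% may be missing.

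**Step 4: how much imputation can restore.** Suppose auxiliary data such as t1 FMI explain a share R² of the variance of the missing scores, and data are missing at random. The effective n is about 129 × (1 − m) / (1 − m × R²). At m = 20% this is 103.2/0.95 = 108.6 for R² = 25%, and 103.2/0.90 = 114.7 for R² = 50%. Before baseline adjustment (normal approximation), power is about 85 to 86% at 20% missing, 81 to 84% at 30% and 75 to 80% at 40%. Part of the loss is recovered, but not all of it.

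**The case against.** The strongest reply is that the design may well keep its power. The primary model adjusts for baseline, which the stated calculation does not appear to use, and with r = 0.5 power stays above 90% at 20% missing. This stands. A reader might infer that the trial is underpowered, and the document does not support that. But the argument rests on a correlation the article never states, and it is not the argument the article makes.

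Second, missing data are not ignored. Imputation is planned, and email and optional phone reminders are used to limit assessment dropout. This also stands. The Statistical analyses section speaks of choosing imputation procedures, and reading it as a claim to identify the missingness mechanism from the data would go too far. Detailed specification of the imputation model can be left to an analysis plan.

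Third, the drop-outs in the sample size sentence may be people who stop the intervention. No inflation is needed for them if d = 0.40 is already an ITT effect. On that reading the sentence is defensible but leaves missing t2 scores unaddressed. The Discussion names assessment dropout explicitly, so the second claim is not rescued.

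Two further inferences are tempting. One is that 40–60% of t2 scores will be missing. That figure in the Discussion is intervention dropout and cannot serve as a missing-data rate. The other is that dropout will be heavier in the intervention arms because waitlist participants have a reason to stay. The Control condition section gives them access after t3 but does not tie it to completing questionnaires, so differential dropout is a possibility and not a documented fact.

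**Conclusion.** The point holds in limited form. Two published statements are wrong in their reasoning: ITT does not make a drop-out allowance unnecessary where t2 scores are missing, and it does not by itself make the estimate unbiased under assessment dropout. On the protocol's own basis, 90% power at 129 per group requires complete t2 FMI. Under the assumed 10 to 40% missing, power runs from about 87% down to 70% unadjusted, from 92% to 78% with r = 0.4, and from 94% to 82% with r = 0.5. These ranges rest on assumed missingness, assumed correlations and the stated d = 0.40, and the table takes no credit for auxiliary data in imputation. Whether 90% is kept cannot be determined from the document. Neither the size nor the direction of any bias can be established from it. The point should be fixed before results are interpreted, but it does not undermine the design.

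**What to change.** 1. In Sample size estimation, delete the sentence saying no allowance is needed. State the power of 129 per arm over a range of missing t2 FMI, for example 10 to 40%, together with the baseline correlation assumed. Trial status reports recruitment as complete, so power is restated and enrolment is not increased.
2. In the Discussion, replace the claim of unbiasedness under assessment dropout with the assumption relied on, for example missing at random given the imputation model.
3. Add one missing-not-at-random sensitivity analysis of the primary outcome, either reference-based imputation from the waitlist distribution or a delta or tipping-point shift, fixed before the data are analysed.

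The cost is revised wording in two places and one extra analysis, with no new participants or measurements. The stated power may become less favourable.

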Finally, the questions of how and for whom exactly mindfulness-based IMIs (as well as IMIs in general) work are yet to be answered [25, 37]. As large-scale RCTs provide an excellent framework for moderation and mediation analyses, they should routinely incorporate such analyses [38]. Therefore, in the current study, we will exploratively examine various potential moderating variables such as sociodemographic variables, pre-treatment symptomatology and treatment expectancy. From theory and current evidence, we also deduced a number of potential variables mediating the effect of mindfulness IMIs on mental health. Those include mindfulness itself [39], cognitive fusion as an aspect of psychological flexibility [39, 40], emotion regulation [41] and clarity about one’s internal experience (operationalized via alexithymia) [42]. Additionally, we will look at self-efficacy, as empowerment and self-management are assumed to be crucial factors for the efficacy of self-help interventions [43].

The current study is an extension of a previous RCT that investigated the efficacy and acceptance of *StudiCare Mindfulness* (StudiCare-M), a guided internet-based intervention to enhance mindfulness and wellbeing in college students [44]. We will examine whether an adapted unguided as well as a GoD version can be effective, as these would offer affordable options for long-term implementation into student health promotion programs. The specific research questions are:
Are the unguided and GoD versions of StudiCare-M effective in enhancing mindfulness in college students compared to a waitlist control group?Are these two versions also effective concerning the secondary outcomes depression, anxiety, stress, presenteeism, well-being and interoceptive sensibility?Are the unguided and GoD versions of StudiCare-M associated with side effects or adverse events?Are there any differences between the unguided and GoD version of StudiCare-M concerning efficacy, adherence, satisfaction, side effects, or adverse events?Which factors are associated with, moderate or mediate the effects of StudiCare-M?

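### The 50% power stated for the exploratory unguided versus guidance-on-demand comparison is about 36% on the two-sided basis behind the section's own sample sizes

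*Protocol article*

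**What the plan says.** All the figures are in the Sample size estimation section of the protocol article.

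- **Comparison with waitlist.** The assumed effect is d = 0.40. The first calculation is described as two-tailed: "Originally, a power analysis based on a two-tailed t-test (calculated using G*Power [93]) resulted in a sample size of 133 participants per group". The revised one allows for clustering by university with ICC = .02: "This calculation indicates that 129 participants per group are required to obtain a power of 1-beta = 90"% at α = .05.
- **UG versus GoD.** The planned sample is called sufficient for this comparison, which is labelled exploratory. The target difference, d = 0.20, is described "as minimal clinically important effect difference with a power of 50% and a significance level of"; the level then given is .05. No sidedness is given here.

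The Statistical analyses section adds "Significance level for all analyses will be defined as alpha = .05", again without sidedness. The fourth research question in the Introduction is worded without direction: "Are there any differences between the unguided and GoD version of StudiCare-M concerning efficacy, adherence, satisfaction, side effects, or adverse events".

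**The concern.** The two power statements stand in consecutive paragraphs, share the same 129 per arm and the same α, and would naturally be read on the same basis. On that basis the second does not follow from the sample size.

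The figure matters because 0.20 is the protocol's own smallest difference of clinical importance between the versions, and the sample is called sufficient to detect it. Whether minimal guidance adds anything bears on the resource argument for the trial. If the UG versus GoD difference is not significant, a reader who relies on the stated power will give that result more weight than the design supports.

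**Working it through.** **Inputs from the document:** 129 per arm (133 in the superseded calculation), 1:1:1 allocation, α = .05, d = 0.40 against waitlist with 90% power, d = 0.20 between versions with 50% power, ICC = .02.

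**Step 1. Find the sidedness behind the section's sample sizes.**

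n per arm = 2 × [(z for α + z for power) / d]²

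- Two-sided, d = 0.40, 90% power: 2 × [(1.960 + 1.282) / 0.40]² = 131.3. With the t distribution, 133 per arm gives 90.1%, so the protocol's 133 is reproduced.
- Multiplying by (1 − ICC): 131.3 × 0.98 = 128.7, rounded up to 129. The revised figure is reproduced. The document does not show this formula; the factor 0.98 is inferred because it gives the stated number.
- One-sided, d = 0.40, 90% power: 108 per arm. This matches neither 133 nor 129.

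Both sample sizes are therefore two-sided.

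**Step 2. Power for UG versus GoD at d = 0.20.**

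Noncentrality = d / √(2/n) = 0.20 / √(2/129) = 0.20 / 0.1245 = 1.606, with df = 2 × 129 − 2 = 256. Power comes from the noncentral t distribution.

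| Basis | 129 per arm | 129, variance × 0.98 | 133 per arm |
|---|---|---|---|
| Two-sided α = .05 | 36.0% | 36.6% | 36.9% |
| One-sided α = .05 | 48.3% | 48.9% | 49.3% |

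The stated 50% is approached only in the one-sided row. Two-sided, the gap is 50 − 36 = 14 percentage points, too large to be rounding.

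**Step 3. What two-sided 50% would require.** Either about 194 per arm at d = 0.20 (193 by the normal approximation), or d of about 0.245 at 129 per arm. At 129 per arm, 80% power is reached at d of about 0.35.

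**Step 4. Could the planned baseline adjustment explain the 50%?** The analysis model includes the baseline value, but the document gives no baseline–outcome correlation r. Taking r as an assumption and multiplying the variance by (1 − r²), two-sided, 129 per arm, t distribution:

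| Assumed r | Power at d = 0.20 | Power at d = 0.40 |
|---|---|---|
| 0.3 | 39% | 92% |
| 0.4 | 42% | 94% |
| 0.5 | 46% | 96% |
| 0.55 | 48% | 97% |
| 0.6 | 52% | 98% |

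A correlation of about 0.55 to 0.6 brings the UG versus GoD figure to around 50%. The same correlation puts the comparison with waitlist at 97 to 98%, not the stated 90%. So adjustment does not explain both figures together.

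**Step 5. Precision.** The 95% confidence interval for an unadjusted standardized difference at 129 per arm has a half-width of about 1.969 × 0.1245 = 0.245, which is wider than the 0.20 of interest.

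**The case against.** The strongest reply is that the figure is not simply wrong. The label two-tailed belongs to the waitlist calculation only, and α = .05 is set without sidedness. A one-sided test gives 48 to 49%, which could fairly be rounded to 50%. A directional hypothesis would be understandable, since the Introduction cites evidence that guided interventions do better. This stands as the likely origin of the number. It does not remove the problem: the section would then change sidedness between paragraphs without saying so, for a research question with no direction. The Introduction also reports that the two previous GoD trials found no significant difference from unguided versions.

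It is also fair that 36% describes an unadjusted test, whereas the planned model adjusts for baseline. The realized power may be higher. But no correlation is stated, and the waitlist calculation takes no credit for one.

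The consequences are limited. The comparison is declared exploratory, the Discussion promises only preliminary evidence, and a stated 50% already signals weak power.

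Three stronger readings are tempting but unsupported:

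- **That 0.20 contradicts the assumed 0.40.** The 0.40 is the effect of each version against waitlist. The 0.20 is the smallest difference between versions worth detecting, not an expected gap. A plan may assume equal effects and still state which gap it could detect.
- **That the unguided arm is underpowered against waitlist.** The section cites g = 0.22 for unguided interventions and gives its reason for assuming more, namely persuasive design features in both versions. Disagreeing with that is a matter of judgement, not an error in this power figure.
- **That a null result will be reported as equal efficacy.** Nothing in the document says so. The risk lies in how readers would use the claim of sufficiency.

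**Conclusion.** The concern holds for the power figure, its unstated sidedness and the claim of sufficiency. On the two-sided basis that reproduces both 133 and 129 per group, power for UG versus GoD at d = 0.20 is about 36%, roughly 14 points below the stated 50%. The chance of missing a true difference of that size is about 64%, not one in two.

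This rests on a two-sided α of .05, no baseline adjustment, complete data from 129 per arm and equal allocation. If the comparison was meant to be one-sided, 50% is close to right, but the document would have to say so and justify the direction.

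Severity is minor to moderate. The 129 per arm comes from the comparison with waitlist, so neither the sample size nor the primary analysis is affected.

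**What to change.** In Sample size estimation, replace the power statement for UG versus GoD with wording such as: *With 129 participants per arm, the exploratory UG–GoD comparison has about 36% power (two-sided α = .05, unadjusted) for d = 0.20; 50% power is reached at d of about 0.245 and 80% at d of about 0.35.* Delete the word *sufficient*.

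State that GoD minus UG will be interpreted through the standardized mean difference with 95% confidence interval, which the Statistical analyses section already plans, and that a non-significant difference will not be taken as evidence of equal efficacy.

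The cost is a change of wording and a less favourable stated figure. No further participants or analyses are needed.
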